### Outcome assessment

The outcome assessment will be at 1, 3, 6, 9 and 12 months post discharge. Assessors will not be allowed to view the cell phone of the participant and they will be instructed not to ask participants the following question: “Did you watch any videos on stroke?” They will be trained to accept random quality cross checks. A random cross check will be done of assessor quality by asking 30 % of the participants if they were asked the above question on assessments. Since our outcome assessment will be blinded and, if an unblinding/protocol violation has occurred at the assessor level, the participant will be removed from the final analysis to avoid assessor bias that may shift the outcome in favor of the intervention.

At an assessment visit:A detailed questionnaire will be filled out which will collect information on:Medication adherenceHistory of hospitalizations since discharge, with any of the stroke complications and associated mortalityKnowledge level of stroke survivor/caregiverStroke survivors will have blood pressure measurement, two separate readings at least 10 minutes apart, at resting and in sitting positionsParticipants will be asked to give blood samples for serum cholesterol, fasting blood sugar and HbA1c (if diabetic) at 6 and 12 months post discharge

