**Methods:**

Movies4Stroke will be a randomized control, outcome assessor blinded, parallel group, single center superiority trial. Participants with an acute stroke, medically stable, with mild to moderate disability and having a stable primary caregiver will be included. After obtaining informed consent the stroke survivor-caregiver dyad will be randomized. Intervention participants will have the movie program software installed in their phone, desktop, or Android device which will allow them to receive, view and repeat 5-minute videos on stroke-related topics at admission, discharge and first and third months after enrollment. The control arm will receive standard of care at an internationally accredited center with defined protocols. The primary outcome measure is medication adherence as ascertained by a locally validated Morisky Medication Adherence Scale and control of major risk factors such as blood pressure, blood sugar and blood cholesterol at 12 months post discharge. Secondary outcome measures are post-stroke complications and mortality, caregiver knowledge and change in functional outcomes after acute stroke at 1, 3, 6, 9 and 12 months. Movies4Stroke is designed to enroll 300 participant dyads after inflating 10 % to incorporate attrition and non-compliance and has been powered at 95 % to detect a 15 % difference between intervention and usual care arm. Analysis will be done by the intention-to-treat principle.

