### Statistical analysis plan

Analysis will be performed on the basis of initial treatment allocation; that is the intention-to- treat (ITT) principle.

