While there is a relative lag in development of such centers, we plan to test and leverage our existing mobile infrastructure as a means of providing continuous care. Based on the current statistics by the Pakistan Telecommunication Authority, mobile phone users in Pakistan were recorded to number greater than 137 million and total cellular density had reached 77 % by 2014 [35]. In addition, mobile brands have introduced cheap Android Smart phones that are rapidly becoming mainstream and are expected to take over the larger market share, with the cheapest Smart phone starting from around US$6 [25]. Thus, we developed this interactive Android application.

mHealth applications have tremendous potential for chronic disease support. However, these software applications have not been tested in rigorous trial designs with clinically meaningful outcomes [36–38, 39].

The strength of this study is the use of a rigorous randomized controlled trial (RCT) design, measurement of intervention usage and fidelity, intervention delivery that is present both within the hospital and at follow-up, evaluation of clinically important outcomes and ITT analysis [40].

The limitations include the following: selection bias: this is a single center study chosen because of the fact that this site provides a standard of care that is algorithmic and replicable; thus, any results may be attributed to the intervention. In this study we may report its efficacy, but the performance in different sites may vary; contamination bias: in an educational intervention, care will have to be taken to avoid contamination of the non-intervention arm with the intervention. To ensure this, videos will be shown in a separate room, and not at the bedside. Given the fact that families do share information, contamination is possible; however, most stroke participants are on different schedules for visits, rehabilitation times, etc. and so we expect less contamination than in areas where a lot of time is spent together by families; attrition bias: many participants may drop out due to the longitudinal nature of the study. To counteract this, trained health care providers will try to follow the subjects closely through regular phone calls and build good rapport with them. A Stroke Helpline number will also be provided.

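### Removing participants whose assessor was unblinded from the final analysis contradicts the planned intention-to-treat analysis

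*Protocol article*

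**What the plan says.** The commitment to intention-to-treat appears three times in the protocol article:

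- Abstract, Methods: "Analysis will be done by the intention-to-treat principle".
- Statistical analysis plan: "Analysis will be performed on the basis of initial treatment allocation; that is the intention-to- treat (ITT) principle".
- Discussion, among the strengths: "evaluation of clinically important outcomes and ITT analysis".

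The Outcome assessment section sets a different rule: "if an unblinding/protocol violation has occurred at the assessor level", then "the participant will be removed from the final analysis to avoid assessor bias that may shift the outcome in favor of the intervention".

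The same section names two things that assessors must avoid. One concerns the phone: "Assessors will not be allowed to view the cell phone of the participant". The other is asking participants whether they have watched stroke videos. Compliance is monitored in a sample: "A random cross check will be done of assessor quality by asking 30 % of the participants if they were asked the above question". No other systematic detection is described.

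**The concern.** The removal rule acts on randomised participants because of something that happens at a follow-up visit. Once participants leave the analysis for such a reason, the arms compared are no longer the arms that were randomised, and the protection that intention-to-treat gives is lost for both primary endpoints (medication adherence and risk factor control).

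The risk is greater if the trigger is related to allocation, and here that is plausible. Under the Intervention section the application is installed only on intervention participants' phones. An assessor who sees it, or who hears a participant mention the videos, is therefore almost always dealing with an intervention participant.

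The aim of the rule, to limit assessor bias, is legitimate. The objection is to pursuing it by deleting people from the final analysis.

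**Working it through.** **1. The two instructions side by side.** Analysis by initial allocation requires each randomised participant to be counted in the allocated arm. The Outcome assessment rule takes some of them out of the final analysis. The article does not confine the rule to a secondary analysis set, to the affected visit, or to outcomes that the assessor rates. The contradiction is in the text and needs no arithmetic.

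**2. What is discarded.** Assessments take place at 1, 3, 6, 9 and 12 months. Blood samples are taken at 6 and 12 months (HbA1c if diabetic). As worded, one breach at one visit removes the participant altogether. That includes visits at which blinding held, and LDL and HbA1c values that assessor knowledge can hardly change.

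**3. How a breach would be found.** The described check asks 30 % of participants, and asks only whether the assessor put the forbidden question. It would not pick up a glimpse of the phone or a spontaneous remark.

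**4. Illustration of bias.** The plan gives no figure for this rule, so there is none to reproduce. From the Sample size calculation section: true rates 0.50 (intervention) and 0.35 (control), 150 per arm. Assumptions not in the document: a fraction f of the intervention arm is removed, nobody is removed from control, and those removed have success rate q.

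Observed intervention rate = (0.50 − f·q)/(1 − f)

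| f | q = 0.80 | q = 0.65 | q = 0.35 |
|---|---|---|---|
| 5 % | 0.460/0.95 = 0.484 | 0.4675/0.95 = 0.492 | 0.4825/0.95 = 0.508 |
| 10 % | 0.420/0.90 = 0.467 | 0.435/0.90 = 0.483 | 0.465/0.90 = 0.517 |
| 20 % | 0.340/0.80 = 0.425 | 0.370/0.80 = 0.4625 | 0.430/0.80 = 0.5375 |

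Against the planned 15-point difference, the shift runs from −1.6 to +0.8 points at f = 5 % and from −7.5 to +3.75 points at f = 20 %. At q = 0.50 it is zero.

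**5. Removals from both arms.** The formula can be written as p + [f/(1 − f)]·(p − q). With the same f in each arm, the shift in the difference is [f/(1 − f)]·[(0.50 − q₁) − (0.35 − q₀)], where q₁ and q₀ are the success rates of those removed. Equal removal counts therefore protect the comparison only if those removed depart from their own arm's rate by the same amount. Example with f = 10 %: q₁ = 0.80 and q₀ = 0.65 give 0.467 − 0.317 = 0.15, no bias. With q₁ = 0.80 and q₀ = 0.35 the result is 0.467 − 0.35 = 0.117.

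**6. How large f might be.** If removals came only from the 30 % check, f = 5 %, 10 % and 20 % would need violations in 0.05/0.30 = one sixth, one third and two thirds of the checked intervention participants. The document gives no violation rate, so the upper rows are not forecasts.

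**7. Power when there is no bias.** Pooled two-sided Z test, α = 0.05 assumed because the sample size section does not state it. Power = Φ[(0.15 − 1.96·SE₀)/SE₁], with SE₀ the pooled and SE₁ the unpooled standard error.

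- 150 v 150: SE₀ = 0.0571, SE₁ = 0.0564, power 75.0 %.
- 135 v 150 (10 % of the intervention arm removed): SE₀ = 0.0586, SE₁ = 0.0580, power 72.8 %.
- 120 v 150 (20 % removed): SE₀ = 0.0604, SE₁ = 0.0600, power 70.1 %.

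The baseline of 75.0 % does not match the stated power of at least 95 %. That is a separate matter, and this point does not depend on it.

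**The case against.** The best defence is that the trigger lies with the assessor and not with the participant. The forbidden question can be put in either arm, a control participant's answer of no also reveals the allocation, and the 30 % check is not limited to one arm. Removals found that way follow assessor behaviour and could be roughly balanced. This stands, and it limits what can be claimed. It does not rescue the rule, because the conflict with intention-to-treat exists even if removals are balanced, and step 5 shows that balance in numbers is not enough.

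A reader might infer several stronger things that the document does not support:

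- *Control participants have nothing to reveal, so the exclusion is certainly arm-related.* The forbidden question contradicts this. Imbalance is a plausible inference from the application being in one arm only.
- *The rule deletes the most engaged intervention dyads and so dilutes the effect.* Nothing in the article says who would be removed, and the described check does not ask about spontaneous disclosure. The direction is open.
- *The data are thrown away for no gain.* Adherence is collected by questionnaire and blood pressure is measured at the visit, so assessor knowledge could affect both. The argument about unaffected data holds for LDL, HbA1c and visits where blinding held.
- *The rule removes no assessor bias at all.* It removes it for the cases that are detected. Detection is partial as described, although the trigger is not expressly restricted to the 30 % check.

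It might also be said that an unseen analysis plan could settle the matter. The protocol article itself states the rule, so the article needs correcting in any case.

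**Conclusion.** The point holds. The protocol article fixes an intention-to-treat analysis and then prescribes an exclusion after randomisation that is incompatible with it. The case rests on that contradiction and not on the illustrative figures.

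The size and sign of any bias cannot be determined from the document. Under one-arm removal and the assumed values of q, the shift is at most 1.6 points at f = 5 % and up to 7.5 points, half the planned difference, at f = 20 %. It can go either way. If those removed are typical of their arm, the cost is power only, about 2 percentage points at 10 % removal and 5 at 20 %, from a baseline of 75.0 %.

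**What to change.** Delete the removal rule from the primary analysis and state that every randomised participant is analysed in the allocated arm. Record each assessor-unblinding event or violation, and report the counts by arm and visit. Add one sensitivity analysis that excludes the affected assessor-rated assessments (adherence and blood pressure at that visit) but keeps the participant, the other visits and the laboratory results.

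The cost is a changed sentence, a recorded item per visit and one extra analysis. Moving the participant to another blinded assessor for later visits is not needed for this fix and would be an operational commitment. The downside is that some possibly biased assessor-rated values stay in the primary analysis. The sensitivity analysis and the reported counts show how much that matters for the events that are detected.

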### Primary study outcomes

All participants will be assessed for outcomes at 1, 3, 6, 9 and 12 months post discharge. The two arms will be compared with respect to:Proportion of participants adhering to medications prescribed (definition of adherence – use of prescribed medications on at least 5 days a week and measured by the locally validated Morisky Medication Adherence Scale [14]Proportion of participants achieving control of blood pressure (control is defined as BP <125/85), blood sugar (HbA1c <7 %) and blood cholesterol (LDL <100 mg/dl) [14]

### Secondary study outcomes

Change in knowledge of caregivers concerning stroke risk factors, stroke rehabilitation and medications (a knowledge questionnaire will be administered at 1, 3, 6, 9 and 12 months post discharge and change in score will be ascertained)Readmission to hospital with any of the stroke-related complications – urinary tract infection, pneumonia, and deep venous thrombosis (this information will be elicited at the follow-up time, based on recall. All participants will be asked to bring documents related to any hospital admissions in the period following discharge)Stroke-related mortality will be assessed through a Verbal Autopsy Scale adopted from the WHO [15]Change in functional outcome (severity and disability after stroke) from baseline among stroke survivors will be assessed through validated tools (NIHSS, Barthel Index and mRS) [16]Level of satisfaction with the intervention and acceptability of mHealth innovation such as videos on selected topics among stroke survivors and caregiver dyads to improve clinical outcomes. This will be done on a self-designed tool which ascertains the constructive and unpleasant attributes of using this mHealth technology (please refer to Form C, Data Collection Form for Stroke Survivors– see Additional file 1). This self-designed tool will be administered by a research supervisor who will be unblinded to the randomization group. This tool has design attributes based on Rogers’ Diffusion of Innovation Theory for ease, adoption, repeatability, and adaptability [17].

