## Background

The World Health Organization (WHO) defines stroke as “a focal (or at times global) neurological impairment of sudden onset, and lasting more than 24 hours (or leading to death) and of presumed vascular origin” [1]. Two thirds, i.e., 36 million of the estimated 56 million deaths worldwide are attributed to non-communicable diseases (NCD), primarily stroke. Over 80 % of strokes now occur in LMICs [2], with 15 million strokes occurring annually worldwide, leaving five million dead, and five million permanently disabled. One person suffers a stroke every 45 seconds; one person dies of a stroke every 4 minutes [3]. Globally, stroke accounts for 46.6 million disability adjusted life-years (DALYs) [4].

NCD and stroke are becoming an important issue in Pakistan as the country undergoes demographic transition [5]. Pakistan, the sixth most populous nation in the world, has a distinctively stroke-prone population. Today, about one in four adult Pakistanis has hypertension and/or diabetes, heart disease, or a stroke equivalent [6]. Yet, early detection and risk reduction would have prevented stroke in 80–90 % of victims [7]. A local study conducted on one ethnicity (Pashtoon), reported a prevalence of 4.8 %, which would translate into four million persons in a country of 180 million [6]. In another hospital-based study, 65 % of adult Pakistani stroke survivors reported at least one post-stroke complication and a 12 % mortality in the first year post discharge [8].

This high-risk population is also highly underserved. Health systems are acutely responsive and are not equipped to respond to chronic diseases. There is not a single inpatient comprehensive rehabilitation system. Since the recent democratic reforms and 18th Constitutional Amendment, an opportunity has arisen for health reform, where devolution has resulted in provincial autonomy for health [9]. Thus, evidence for a systematized, replicable, scalable and effective response to chronic disorders is much more likely to be adapted.

In 80 % of stroke victims, further events may be prevented by altering lifestyle risk factors, and increasing adherence to medications to control hypertension, diabetes and hyperlipidemia [10–12]. However, there exists an implementation gap to adopt widely recognized beneficial medicines and lifestyle changes after stroke [6].

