### Sample size calculation

The study is designed to enroll 300 participant dyads (150 participants and 150 caregivers in each group – intervention versus standard care) after inflating 10 % to incorporate attrition and non-compliance. The sample size was calculated keeping in mind the two primary end-points of medication adherence and risk factor control; the primary end-point that gave the highest sample size was kept as the final sample size. This number of participants would provide the study with the ability to detect a 15 % difference among groups with a power of at least 95 %. The proportion of participants achieving control of three modifiable risk factors (blood pressure, blood cholesterol and blood sugar) was assumed to be 0.50 in the treatment group and 0.350 in the control group. The test statistics used was a two-sided *Z* test. The sample size was calculated using NCSS PASS (version 2008).

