### Secondary end-points

To analyze the secondary outcome, caregivers’ mean score of knowledge regarding stroke risk factors, stroke rehabilitation and medications at each follow-up visit between the two groups will be calculated through Student’s *T* test if the outcome is symmetrically distributed or the Mann-Whitney *U* test if the outcome is not symmetrically distributed.

The proportion of participants with respect to readmission to hospital with any of the stroke-related complications between the two groups will be calculated either by Pearson’s chi-square test or Fischer’s exact test (if the expected cell count is less than 5).

The proportion of participants with respect to stroke-related mortality between the two groups will be calculated either by Pearson’s chi-square test or Fischer’s exact test (if the expected cell count is less than 5).

The change in mean score of National Institutes of Health Stroke Scale (NIHSS), Barthel Index and mRS from baseline at each follow-up visit between the two groups, will be calculated through Student’s *T* test if the outcome is symmetrically distributed or the Mann-Whitney *U* test if the outcome is not symmetrically distributed.

The change in mean scores for level of satisfaction with the intervention and acceptability of mHealth innovation at the third month follow-up visit post discharge between the two groups will be calculated through Student’s *T* test if the outcome is symmetrically distributed or the Mann-Whitney *U* test if the outcome is not symmetrically distributed.

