### Intervention

Intervention consists of:-5-minute videos, on various stroke-related topics/themes delivered at the time of enrollment into the study, before discharge from the hospital, at first and third month follow-up post dischargeSession 1 will be delivered at the time of enrollment into the study and will cover themes on information for caregivers including recognition of stroke, and different skills will be taught to the caregivers including swallowing exercises, different rehabilitation exercises and naso-gastric tube feedingSession 2 will be delivered at the time of discharge from the hospital and will include videos on emergency preparedness – cardiopulmonary resuscitation, seizures, heart attack, hypoglycemia and recurrent strokeSession 3 will be delivered at first month follow-up post discharge and will include videos on frequently used medications by stroke survivors, such as anticoagulant, antihypertensive and lipid-lowering drugsSession 4 will be delivered at third month follow-up post discharge and will include videos on secondary stroke prevention (recurrent attack) – exercise, physical activity, recognition of depression, diet modification and accurate measurement of blood pressure and blood sugarPlease refer to Additional file 4 (Video Thematic Intervention Chart) which demonstrates the core messages that will be delivered in the videosDiscussion and question and answers after viewing each set of videos to ensure that the core message has been understood and there are no lacunae in understanding the message imparted by the videos, which may be re-wound and re-run for those who could not understand a particular messageMovies4Stroke Application Installation in a memory card – a memory card containing the movies application will be installed in the participants’ cell phones in the intervention group to ensure that the videos can be replayed at home to refresh the memory of various details which may not have been captured in the mandatory viewing session that captures the usage data

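### The only defined mortality comparison is stroke-related death by verbal autopsy, and its cause label could differ by arm because only intervention caregivers receive video training in recognising stroke and other acute events

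*Protocol article*

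**What the plan says.** The Secondary objective, Secondary study outcomes and Secondary end-points sections all restrict mortality to stroke-related death. For ascertainment, the protocol says: "Stroke-related mortality will be assessed through a Verbal Autopsy Scale adopted from the WHO". For analysis, it says: "The proportion of participants with respect to stroke-related mortality between the two groups will be calculated either by Pearson’s chi-square test", with Fisher's exact test when expected counts are small. None of these sections defines an all-cause comparison.

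Under Intervention, session 1 "will cover themes on information for caregivers including recognition of stroke". Session 2 covers emergencies: seizures, heart attack, hypoglycemia and recurrent stroke. The section on compliance during administration has the study officer make sure that the caregiver watches every video at least once. The Caregiver definition describes someone who is with the survivor around the clock.

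The Outcome assessment section provides for blinded assessors and for random cross-checks of their conduct. Its visit questionnaire asks about hospitalisations with stroke complications and mortality associated with them.

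**The concern.** A cause-specific death outcome needs two facts: that the participant died, and why. The first is the same fact whoever reports it. The second, under verbal autopsy, is built from someone's account of the final illness. Here the randomised treatment trains the likely informant in one arm to recognise the events that decide the classification. The intervention may then change the measurement of the outcome as well as the outcome itself, and a difference in stroke-related death could not be separated from a difference in reporting. Caregiver knowledge is itself a secondary outcome, so the better the videos work on knowledge, the more the informants in the two arms may differ.

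At stake is the interpretation of one secondary result. Adherence and risk-factor control do not pass through this instrument.

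**Working it through.** The protocol gives no event rate or power for mortality, so there is no stated figure to reproduce. The check has two parts.

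**Which facts depend on the informant**

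- Respondent: not named. That it is the caregiver is an inference from the nature of a verbal autopsy and from the Caregiver definition.
- Training: the video content on stroke and on other acute events is given to the intervention arm only. The standard-of-care section gives all participants counselling, including on possible complications, but does not list stroke recognition.
- Blinding: it applies to the assessor. An intervention caregiver has watched the videos and cannot be blinded to them.
- Direction: stroke-recognition teaching could raise the share of deaths labelled stroke-related. Teaching on heart attack, seizures and hypoglycemia could lower it.

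**How large the distortion could be (illustration)**

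Inputs from the document:
- "a 12 % mortality in the first year post discharge", from the Background section (a hospital-based study; cause of death not stated)
- "150 participants and 150 caregivers in each group", from the Sample size calculation section

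Assumptions: true all-cause mortality is 12 % in both arms; the share labelled stroke-related differs by arm; tests are two-sided at 0.05.

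- Deaths per arm: 0.12 × 150 = 18.
- Apparent rate in an arm: label share × 0.12. At 50 %: 0.50 × 18 = 9 deaths, 9/150 = 6.0 %. At 70 %: 0.70 × 18 = 12.6 deaths, 12.6/150 = 8.4 %. Risk ratio: 8.4/6.0 = 1.4.
- Chance of a nominally significant result in the direction of the shift: Φ[(Δ − 1.96·SE0)/SE1], where SE0 = √[2p̄(1−p̄)/n] and SE1 = √{[p1(1−p1) + p2(1−p2)]/n}.
- For 6.0 % against 8.4 %: Δ = 0.024 and p̄ = 0.072, so SE0 ≈ 0.0298 and SE1 ≈ 0.0298. Then (0.024 − 0.0585)/0.0298 ≈ −1.16, and Φ ≈ 0.124.

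| Label shares | Apparent rates | Risk ratio | Chance, 150 per arm | Chance, 135 per arm |
|---|---|---|---|---|
| 50 % vs 60 % | 6.0 % vs 7.2 % | 1.2 | 6.2 % | 5.9 % |
| 50 % vs 70 % | 6.0 % vs 8.4 % | 1.4 | 12.4 % | 11.5 % |
| 50 % vs 80 % | 6.0 % vs 9.6 % | 1.6 | 21.2 % | 19.5 % |
| 40 % vs 80 % | 4.8 % vs 9.6 % | 2.0 | 36.2 % | 33.1 % |

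The 135 column removes the planned 10 % for attrition (150 × 0.9). The chances count one direction only; with no labelling difference that figure would be 2.5 %. Either arm may be the one with the higher share, so each row can be read in reverse. In every row the all-cause rates are 12 % and 12 %, and the expected difference is zero.

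**The case against.** The strongest reply is that the mechanism rests on an instrument that is not shown. The article does not say who answers, what is asked or who assigns the cause. If a blinded assessor scores a standard scale from structured answers, the caregiver's opinion may carry little weight and the labelling gap would be small. Control caregivers also receive verbal instructions from a multidisciplinary team and a written summary with alerts, so the contrast is not trained against untrained. The label shares above have no source, and the 12 % comes from another cohort. Even at 50 % against 70 %, a falsely significant result would be the exception. Finally, stroke-related death matches the stated objective, and a supplementary all-cause analysis may sit in a document not shown.

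Most of this stands as a limit on size and certainty. It does not remove the point. Assessor blinding cannot correct an account already shaped by what the informant was taught, and the article fixes objective, outcome and test as cause-specific.

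A reader might infer more than the documents support:

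- **That bias is established, or favours one arm.** Neither follows. The respondent is inferred, and the training content could move attribution either way.
- **That counting other deaths as non-events is an error.** Over a fixed follow-up, the proportion with stroke-related death is a valid cumulative incidence, and the planned tests fit it.
- **That the abstract contradicts the methods.** Its unqualified mortality reads as shorthand; the sections that define the outcome agree with one another.
- **That the mortality result will decide the later, larger study.** The Discussion makes that study depend on promising results in general.

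**Conclusion.** The point holds as a modest improvement to a secondary outcome. The protocol's only defined mortality comparison depends on a cause label whose likely informant is trained by video in one arm only, and assessor blinding does not protect that label. The rates compared could differ in either direction when the numbers of deaths are equal.

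The size is unknown. Across the assumed splits the spurious risk ratio runs from 1.2 to 2.0, but these figures show the mechanism and do not predict the result. The conclusion assumes that the caregiver is the respondent and that the respondent's account influences the assigned cause. All-cause death is free of cause attribution, though not of incomplete vital status.

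**What to change.** In Secondary study outcomes and Secondary end-points, add all-cause death as the main mortality comparison by allocated arm. Count deaths over the 12-month post-discharge follow-up plus in-hospital deaths after randomisation. The planned chi-square or Fisher's exact test can be kept. Report verbal-autopsy stroke-related death by arm as supportive, and align the Secondary objective.

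There are two small costs. Vital status must be recorded for every participant at each scheduled contact; the visit questionnaire as described ties mortality to stroke complications, so this is more than a change of wording. All-cause death also includes some deaths that the videos cannot affect, which dilutes any true effect.
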